### Trial design and study setting

The TB SCRIPT trial is a phase 3, single-blinded, multi-center, randomized superiority trial evaluating the clinical impact of POC CRP-based TB screening on immediate and longer-term outcomes of PLHIV in Uganda. Uganda is among the world’s 30 high HIV/TB burden countries with an HIV prevalence of 6.2% and an annual TB incidence of 253 cases per 100,000 [1, 24]; among all TB cases, HIV prevalence is estimated at 45% [25]. Data from the 2014–2015 national TB prevalence survey estimate that half of all TB cases go undiagnosed each year, and the overall TB burden is greatest in urban areas [24].

We will randomize 1720 PLHIV presenting for routine ART initiation in three clinics (two public and one non-government/non-profit) in Kampala, Uganda, to either POC CRP-based TB screening (intervention) or symptom-based TB screening (control) with a 1:1 allocation ratio over a 2-year period. After randomization, we will perform baseline TB screening in accordance with the participant’s assigned TB screening strategy. Based on the results of baseline TB screening, we will either collect clinical specimens (urine, sputum) for confirmatory TB testing (urine lipoarabinomannan [LAM], sputum Xpert Ultra MTB/RIF, if screen-positive) or assess 3HP eligibility (if screen-negative, Fig. 1). Supported by study staff, clinic staff will provide all further care and follow-up for HIV, 3HP, and/or active TB, per routine clinic protocols. We will subsequently extract relevant clinical and outcome data from the clinic medical record at regular intervals (months 3, 6, 12, 18, and 24) for 2 years and collect sputum specimens for comprehensive TB testing (sputum Xpert Ultra, culture and drug susceptibility testing [DST]) at the final (24 months) study visit to ascertain 2-year active TB status.

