##### Screen-positive participants

We will collect spontaneously voided urine and spot sputum specimens (induced, if necessary) from all screen-positive participants (POC CRP ≥8 mg/L in the intervention arm; presence of ≥1 symptom in the control arm) for urine LAM (Alere Determine TB-LAM) and sputum Xpert Ultra testing. In accordance with current WHO guidelines, sputum Xpert Ultra testing will be performed if (1) urine LAM is negative or (2) urine LAM is positive and the participant has risk factors for drug-resistant TB (prior TB treatment, contact with drug-resistant TB case). Participants who test positive for TB by urine LAM and/or sputum Xpert Ultra will be referred to clinicians for TB treatment initiation. To maximize real-world relevance, sputum will not be submitted for mycobacterial culture because most HIV programs in high burden countries use Xpert (standard cartridge or Ultra) as the confirmatory test for TB. Participants who screen-positive but test negative by urine LAM and sputum Xpert Ultra will not be given 3HP at the time of enrollment (as their risk of active TB remains non-negligible), but will be eligible for TPT initiation at the discretion of treating (non-study) clinicians throughout the follow-up period.

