### Outcomes

The primary trial endpoint is a composite outcome of microbiologically confirmed incident TB and all-cause mortality, measured as time to first diagnosis of incident TB or death from any cause. Microbiologically confirmed incident TB is defined as active TB diagnosed by either culture, one non-trace positive Xpert Ultra result or two trace-positive Xpert Ultra results, or positive urine LAM result from 3 months after randomization to the end of follow-up (at 2 years, or at the time of last contact for participants who are lost to follow-up). To assess active TB status at the end of follow-up, 2 spot sputum specimens will be collected from all participants who have not taken anti-TB treatment during the study at the final (24 months) study visit for sputum Xpert Ultra testing, liquid culture, and drug susceptibility testing (for participants who received any TPT). Secondary outcomes are presented in Table 2.

**Table 2 Tab2:** Secondary outcomes of the TB SCRIPT trial

Outcome	Numerator	Denominator

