**A. TB incidence**		
Number diagnosed with microbiologically confirmed incident TB within 2 years	# diagnosed with incident TB (incident TB = positive non-trace Xpert Ultra result, two trace Xpert Ultra results, or ≥ 1 positive culture result > 3 months after study entry)	None
2-year incidence of microbiologically confirmed TB	# diagnosed with incident TB	# randomized to corresponding study arm - # treated for prevalent TB (prevalent TB = active TB diagnosed ≤3 months of study entry)
Time to microbiologically confirmed incident TB diagnosis	Days from 3 months post-enrollment to incident TB diagnosis (or censoring)	
Incident rate of microbiologically confirmed TB	# diagnosed with incident TB	(# randomized to corresponding study arm - # treated for prevalent TB)/time in person-years
Number diagnosed with drug-resistant incident TB within 2 years	# diagnosed with incident drug-resistant TB (drug-resistant TB = DST-detected resistance to drugs administered for TPT [e.g., isoniazid])	None
2-year incidence of drug-resistant TB among people receiving TPT	# diagnosed with incident drug-resistant TB	# received TPT of any duration

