#### Final TB status assessment

For all participants who have not taken anti-TB treatment during follow-up, we will collect 2 spot sputum specimens at the final (24 months) study visit for sputum Xpert Ultra testing; repeat Xpert Ultra testing, if the initial test is trace-positive; and liquid culture and drug susceptibility testing (DST). Speciation testing will be performed on all positive cultures to confirm the presence of *M. tuberculosis* complex using Ziehl-Neelsen smear microscopy for detection of acid-fast bacilli and SD MPT64 (Standard Diagnostics Bioline TB Ag MPT64, South Korea) for rapid *M. tuberculosis* antigen detection. DST will include susceptibility testing to all first-line TB medications including isoniazid and rifamycin-based drugs. Participants will be classified as having incident TB if at least one of the following criteria are met: at least one sputum culture positive for *M. tuberculosis* complex, one non-trace-positive Xpert Ultra result, or two trace-positive Xpert Ultra results.

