### Statistical methods

#### Primary and secondary outcomes

The primary trial outcome is a 2-year composite endpoint of microbiologically confirmed incident TB and all-cause mortality, measured as time to first diagnosis of incident TB or death from any cause. The primary analysis will be by intention-to-treat (ITT), including all participants randomized without regard to the results of baseline TB screening, and we will use a two-sided alpha (0.05 significance) in assessing the effect of the intervention on the primary outcome. Participants with prevalent TB will be included in the analysis to preserve the randomized groups (the ITT principle) but excluded from the outcome of incident TB because subsequent disease is more likely to represent relapse or failure (and these participants will not routinely receive TPT). Time from randomization to first event (diagnosis of incident TB or death from any cause) will be analyzed using the log rank test and Cox proportional hazards models, adjusted for the study site. If data are missing or a patient is lost to follow-up, a patient’s data will be censored in the analysis at the date of last known contact. We will also use the Mantel-Haenszel method to determine standardized incidence rates and incidence rate differences. Balance at baseline on all known and suspected prognostic factors will be assessed, and if important imbalances are found (e.g., differences in median baseline CD4 count), a sensitivity analysis will be conducted using a Cox model to adjust for these factors. We will also assess the impact of clinician-initiated co-interventions (e.g., clinician-initiated TPT, clinician-initiated TB treatment) on the primary outcome. We will conduct a sensitivity analysis in which these participants are censored as soon as they are initiated on TPT or TB treatment by non-study clinicians. Standard checks for variation by enrollment site will also be planned. Secondary outcomes for the primary objective include the individual primary endpoints (TB incidence and mortality analyzed separately) and 2-year isoniazid-resistant TB incidence and will be analyzed using a similar approach; there will be no adjustment for multiplicity since these are pre-specified secondary outcomes.

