We will repeat the primary analysis in the following pre-specified sub-groups: by age, gender, enrollment site, and CD4 strata (< 50, 50–199, ≥200 cells/μL). Safety data related to missed diagnoses of prevalent TB, acquired drug-resistant TB, and TPT-related serious adverse events will be tabulated by study arm.

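### Month-24 drug susceptibility testing is limited to TPT recipients in one section but not in three others; if the limit were applied, the arm-level count of resistant TB would be tilted against the CRP arm

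*Protocol article*

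**What the plan says.** The protocol article describes DST at the 24-month visit in four places.

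- **Outcomes:** "drug susceptibility testing (for participants who received any TPT"). This is the only place with a TPT condition.
- **Final TB status assessment:** the sampling rule here reads "For all participants who have not taken anti-TB treatment during follow-up, we will collect 2 spot sputum specimens at the final (24 months) study visit". After a first Xpert Ultra, the further tests listed are "repeat Xpert Ultra testing, if the initial test is trace-positive; and liquid culture and drug susceptibility testing (DST"). The only condition is no anti-TB treatment during follow-up.
- **Trial design and study setting:** "comprehensive TB testing (sputum Xpert Ultra, culture and drug susceptibility testing [DST]) at the final (24 months) study visit".
- **Table 1:** a DST row at month 24 with no condition, although other rows of the table do carry conditions (liver enzymes, baseline Xpert Ultra).

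Resistance is then used as follows.

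- **Table 2, part A:** a case is drug-resistant only if DST detects resistance to a drug given for TPT. One row is a count per arm with no denominator. A separate row is the "2-year incidence of drug-resistant TB among people receiving TPT".
- **Statistical methods:** the secondary outcomes include "2-year isoniazid-resistant TB incidence and will be analyzed using a similar approach". Among the safety data, "acquired drug-resistant TB, and TPT-related serious adverse events will be tabulated by study arm".
- **Data monitoring committee:** the DMC sees cumulative TB incidence, including drug-resistant TB, with closed-session tables by arm.

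**The concern.** The document states two different populations for one laboratory test, and the outcome depends on which applies. Under the Outcomes wording, a participant who never received TPT cannot be recorded as having resistant TB from the month-24 visit, whatever the isolate would show. TPT receipt is a post-randomization variable, and the intervention is meant to raise it. The chance of detecting resistance would therefore differ between arms by construction.

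At stake is the reading of a safety-relevant secondary outcome. The section on risks to participants names acquired resistance as the potential harm of starting 3HP in missed TB. An apparent excess in the CRP arm that came only from unequal testing could mislead the DMC and readers of the trial.

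**Working it through.** **Plan figures.** The document gives no figure for resistance. The planning numbers borrowed below reproduce:

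- Evaluable per arm: 860 × (1 − 0.12) = 756.8.
- Composite events: 756.8 × 0.125 = 94.6 (plan: 95) and 756.8 × 0.081 = 61.3 (plan: 62).
- Power of a two-sided 0.05 two-proportion test at 756.8 per arm: 0.800 to 0.805 (plan: 80%).

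**Inputs (Sample size section).** 3HP initiation of 55% in the CRP arm and at most 15% in the control arm; 860 per arm; control 2-year TB incidence 7.3%.

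**Step 1: who could have a DST result under the restriction.**

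- CRP: 860 × 0.55 = 473.
- Control: 860 × 0.15 = 129 at most.
- Coverage ratio: 473 / 129 = 3.67.

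Without the restriction the coverage ratio is 1.00.

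**Step 2: allow for clinician-initiated TPT.** The restriction refers to any TPT, and the section on screen-positive participants lets routine clinicians start it. No rate is given, so the control share is varied by assumption with CRP held at 55%:

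| Control share receiving TPT | Coverage ratio |
|---|---|
| 15% | 0.55 / 0.15 = 3.67 |
| 25% | 0.55 / 0.25 = 2.20 |
| 35% | 0.55 / 0.35 = 1.57 |
| 45% | 0.55 / 0.45 = 1.22 |
| 55% | 1.00 |

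**Step 3: from coverage to detected cases.** Let r be the share of TB cases that are resistant (same in both arms), RR the TB risk of TPT recipients relative to non-recipients, and b the risk in non-recipients (same in both arms). For an arm with TPT share t:

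- detected under the restriction ∝ t × RR × b × r;
- detected with everyone tested ∝ (t × RR + 1 − t) × b × r.

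In the CRP:control ratio, b and r cancel:

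| RR (assumed) | Restricted testing | Everyone tested |
|---|---|---|
| 1.0 | 3.67 | 1.00 |
| 0.7 | 3.67 | 0.835 / 0.955 = 0.87 |
| 0.4 | 3.67 | 0.67 / 0.91 = 0.74 |

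At 55% versus 15%, restricted testing can thus reverse the direction.

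**Step 4: absolute size.** With RR = 1, TB risk 7.3% in both arms and an assumed r of 10%:

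- CRP: 756.8 × 0.55 × 0.073 × 0.10 = 3.0.
- Control: 756.8 × 0.15 × 0.073 × 0.10 = 0.8.
- With everyone tested: 756.8 × 0.073 × 0.10 = 5.5 in each arm.

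For r of 5% the restricted counts are 1.5 and 0.4; for 20% they are 6.1 and 1.7. These treat every 2-year case as if found by culture at month 24, so for month-24 testing they are upper illustrations under these assumptions. The document does not give the share of cases found at that visit.

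**The case against.** **The bias is conditional.** Three of the four places carry no TPT condition. A reader might infer that the CRP arm will look worse under the plan as it stands. The documents support that only if the parenthesis in Outcomes governs. This stands: the defect is an inconsistency with a biased branch.

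**Month-24 testing is not all testing.** A reader might carry the fold-difference over to all 2-year resistant TB. The restriction applies only to sputum taken at the final visit from people not treated for TB during the study. How earlier cases obtain DST is not stated in either section, and if they are tested regardless of TPT, the overall ratio lies closer to 1. This also stands.

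**The rate among TPT recipients.** A reader might think the restriction distorts this too. It does not, because numerator and denominator are both recipients. It is also the only 2-year incidence of resistant TB in Table 2, so the isoniazid-resistant incidence named under Statistical methods may mean this row. That leaves the per-arm count, the safety tabulation and the DMC tables exposed. The recipient rate has a separate limit: it compares groups formed after randomization.

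**Drugs administered for TPT.** One could say this phrase in Table 2 already confines the outcome to recipients. It names the drugs, not the population; the next row adds the recipient condition separately.

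**Baseline culture.** A reader might infer from "sputum will not be submitted for mycobacterial culture" that this choice is why acquired and transmitted resistance cannot be separated. That sentence concerns screen-positive participants, who are not given 3HP at enrollment. It does not bear on study-initiated TPT recipients and is no part of this point.

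**Importance.** Expected counts are a handful, and the DMC section names missed prevalent TB as the primary risk and safety endpoint. This limits severity but does not remove the contradiction.

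**Conclusion.** The contradiction is real, and one of its two readings ties detection of resistance to the variable that the intervention changes. If the Outcomes restriction were applied, month-24 DST coverage would differ by up to 3.67-fold on the planned 3HP figures, and less as clinicians give TPT to more controls. The direction is against CRP as long as that arm receives more TPT, which is the trial's own hypothesis.

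The coverage ratio rests on the planned 55% and 15%. Carrying it over to detected cases further assumes that recipients in the two arms have the same TB risk and resistance share. The absolute counts rest on assumed resistance shares. The effect is confined to arm-level resistance outcomes with few events; the primary endpoint, alpha and sample size are untouched. Severity: should-fix.

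**What to change.** 1. In Outcomes, delete the parenthesis that limits DST to TPT recipients, so that DST is done on every month-24 culture positive for *M. tuberculosis*, in line with the design section, Table 1 and Final TB status assessment.
2. Under Statistical methods and in Table 2, make isoniazid-resistant incident TB per randomized participant the between-arm comparison.
3. Keep the rate among TPT recipients, with its numerator limited to recipients, and label it a descriptive, non-randomized summary.

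**Cost:** wording, plus DST that Final TB status assessment already plans. The extra tests cannot exceed the planned incident TB cases: 756.8 × 0.073 = 55 in controls and, if the 35% reduction applies to TB, 756.8 × 0.04745 = 36 in the CRP arm. They will be fewer, since only untreated, culture-positive non-recipients at month 24 are added.

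With recruitment from 16 November 2020, month-24 visits fall due from November 2022, so one testing population should be fixed before then. If visits have already taken place, record whether positive cultures from non-recipients were tested.

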**A. TB incidence**		
Number diagnosed with microbiologically confirmed incident TB within 2 years	# diagnosed with incident TB (incident TB = positive non-trace Xpert Ultra result, two trace Xpert Ultra results, or ≥ 1 positive culture result > 3 months after study entry)	None
2-year incidence of microbiologically confirmed TB	# diagnosed with incident TB	# randomized to corresponding study arm - # treated for prevalent TB (prevalent TB = active TB diagnosed ≤3 months of study entry)
Time to microbiologically confirmed incident TB diagnosis	Days from 3 months post-enrollment to incident TB diagnosis (or censoring)	
Incident rate of microbiologically confirmed TB	# diagnosed with incident TB	(# randomized to corresponding study arm - # treated for prevalent TB)/time in person-years
Number diagnosed with drug-resistant incident TB within 2 years	# diagnosed with incident drug-resistant TB (drug-resistant TB = DST-detected resistance to drugs administered for TPT [e.g., isoniazid])	None
2-year incidence of drug-resistant TB among people receiving TPT	# diagnosed with incident drug-resistant TB	# received TPT of any duration

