### Objectives

The primary objective of TB SCRIPT is to compare the impact of POC CRP-based with symptom-based TB screening on 2-year TB disease outcomes. We will randomize participants to either POC CRP-based (intervention) or standard-of-practice symptom-based TB screening (control). All participants who screen positive will undergo confirmatory TB testing, while only participants who screen negative will initiate 12 weekly doses of isoniazid and rifapentine (3HP), a short-course TPT regimen. We will follow all eligible participants for 2 years to assess TB incidence and all-cause mortality. At the final study visit, we will collect sputum to ascertain active TB status from participants who have not been diagnosed with or treated for active TB during follow-up. The primary hypothesis for this objective is that participants randomized to POC CRP-based TB screening will have lower combined 2-year TB incidence and mortality (composite primary trial outcome), relative to participants randomized to symptom-based screening. The second objective is to compare the impact of POC CRP-based with symptom-based TB screening on (1) TPT uptake and (2) prevalent TB case detection, intermediate outcomes on the pathway to the combined primary trial outcome. The primary hypothesis for this objective is that participants randomized to POC CRP-based TB screening will have higher rates of TPT uptake and completion, determined via objective monitoring, and similar rates of prevalent TB case detection relative to participants randomized to symptom-based screening.

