To evaluate intermediate outcomes on the pathway to the composite primary trial outcome, we will determine the proportion of randomized participants initiating TPT (prescribed TPT), the proportion of randomized participants completing TPT (≥90% TPT pills taken), the proportion of randomized participants diagnosed with prevalent TB, and the proportion of randomized participants with prevalent TB completing TB treatment (by clinic record review). The primary analysis will be by ITT, with the outcome of initiating any TPT based on actual events, irrespective of whether the algorithm was followed. Participants eligible for 3HP based on the results of baseline screening (i.e., study-initiated TPT) may decline to initiate 3HP after randomization despite being prescribed 3HP; these participants will be counted as not having started TPT. Participants who were initiated on TPT during study follow-up (i.e., clinician-initiated TPT for participants who were classified as ineligible for 3HP based on the results of baseline screening) will be counted as having started TPT; 6 months of daily isoniazid (IPT) is currently the most common TPT regimen available for routine clinical use. We will compare the proportion of PLHIV initiating any TPT (study- and clinician-initiated TPT) and the proportion of PLHIV completing TPT (the denominator will be the total number of participants in the study arm), calculating the risk difference and 95% confidence intervals (CI) using standard methods, adjusted for study site using Cochran-Mantel-Haenzsel weights. If respective data on an outcome is missing or a patient is lost to follow-up, it will be assumed that the patient did not initiate nor complete TPT (depending on what data are available). Our working hypothesis is that POC CRP-based TB screening will increase the proportion of PLHIV initiating and completing TPT by at least 40%, relative to symptom-based screening. We will compare the proportion of PLHIV with screen-positive prevalent TB and the proportion of PLHIV with screen-positive prevalent TB completing TB treatment, calculating the risk difference and 95% CIs using standard methods, adjusted for study site using Cochran-Mantel-Haenszel weights. Our working hypothesis is that the proportion of PLHIV with screen-positive prevalent TB will be similar in each arm, and we expect the upper bound of the CI of the difference will be no more than 5%. We consider this margin of 5% sufficiently small to conclude equivalence.

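### Drug-resistant TB is defined by the TPT drugs in Table 2 but as isoniazid resistance alone in the analysis text, which leaves out rifamycin resistance without isoniazid resistance

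*Protocol article*

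**What the plan says.** Four parts of the protocol article bear on this outcome.

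- **Definition.** Table 2, part A, counts incident drug-resistant TB, with "drug-resistant TB = DST-detected resistance to drugs administered for TPT [e.g., isoniazid". The next row is "2-year incidence of drug-resistant TB among people receiving TPT", with TPT recipients as the denominator.
- **Analysis.** Statistical methods, Primary and secondary outcomes, lists "2-year isoniazid-resistant TB incidence and will be analyzed using a similar approach". No other drug is named there.
- **Regimens.** Study TPT is "12 weekly doses of isoniazid and rifapentine (3HP), a short-course TPT regimen". Screen-positive participants who test negative may get TPT later from routine clinicians, for whom "6 months of daily isoniazid (IPT) is currently the most common TPT regimen available for routine clinical use".
- **Testing.** Final TB status assessment says "DST will include susceptibility testing to all first-line TB medications including isoniazid and rifamycin-based drugs". On who is tested, Outcomes has "drug susceptibility testing (for participants who received any TPT", whereas Final TB status assessment opens with "For all participants who have not taken anti-TB treatment during follow-up, we will collect 2 spot sputum specimens" and states no TPT condition for DST.

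Acquired resistance also appears in Risks to study participants (prevalent TB put on 3HP), in the safety tabulation by arm at the end of Statistical methods, and in the data monitoring committee's report. None of these three names a drug.

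**The concern.** One secondary outcome has two definitions, and they disagree on rifamycin resistance without isoniazid resistance. Rifapentine is one of the two drugs in 3HP, and the CRP strategy is meant to raise 3HP use sharply. If the analysis text is followed, the laboratory will hold the rifamycin result but the analysed outcome will ignore it unless isoniazid resistance is also present. A harm that the protocol attributes to 3HP would then be measured for only one of its two drugs.

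Table 2 is also open on a second point. It does not say whether the TPT drugs are those used in the trial as a whole or those that the individual participant took.

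**Working it through.** **The plan's own figures.** No figure is stated for the resistance outcome, so there is none to reproduce. The primary sample size does reproduce. With 860 per arm and 12% loss, the effective n is 860 × 0.88 = 756.8 per arm. A two-proportion test (pooled variance, two-sided 0.05) gives power 0.805 for 12.5% against 8.1%, and 0.800 for an exact 35% reduction to 8.125%; the plan states 80%. Nothing below alters this.

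**Which isolates count under each definition.**

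| Isolate | Analysis text | Table 2, one list for the trial | Table 2, participant's own TPT |
|---|---|---|---|
| Isoniazid-resistant only | counts | counts | counts after 3HP or isoniazid alone; undefined without TPT |
| Resistant to both | counts | counts | as above |
| Rifamycin-resistant only | does not count | counts | counts after 3HP; not after isoniazid alone; undefined without TPT |

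The first two columns differ only in the last row. That difference needs no assumption about how Table 2 is read: under either reading, Table 2 counts a rifamycin-resistant, isoniazid-susceptible case in a 3HP recipient, and the analysis text does not.

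**Exposure to a rifamycin as study TPT (shares from Sample size).**
- Control: at most 0.15 × 860 = 129
- CRP arm: 0.55 × 860 = 473
- Ratio: 0.55 / 0.15 = 3.67

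**Number of incident TB cases (Sample size).** Control: 0.073 × 756.8 = 55.2. CRP arm, with the same 35% reduction: 55.2 × 0.65 = 35.9. Not all of these will have a DST result, since Outcomes allows diagnosis by Xpert Ultra or urine LAM without culture.

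**Illustration only.** The protocol gives no resistance rate. Assume that a proportion q of all participants develops incident TB that is rifamycin-resistant and isoniazid-susceptible, equal in both arms and in all TPT groups, with q from 0.1% to 1%, and that every such case has DST. Against a control TB incidence of 7.3%, this is 0.1/7.3 = 1.4% to 1/7.3 = 13.7% of control-arm cases, a deliberately wide range.

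| Rule | Control, cases counted | CRP arm, cases counted |
|---|---|---|
| Isoniazid only | 0 | 0 |
| One list for the trial (860 × q) | 0.9 to 8.6 | 0.9 to 8.6 |
| Participant's own TPT (129 × q; 473 × q) | 0.13 to 1.3 | 0.47 to 4.7 |

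**Who has DST.** If Outcomes governs, participants without TPT have no month-24 DST result and cannot contribute an event from that visit under any drug list. Since TPT uptake is expected to differ widely between arms, the chance of being tested would differ too. If Final TB status assessment governs, this problem does not arise.

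**The case against.** The strongest reply is that the analysis text is shorthand. Outcomes refers the reader to Table 2 for the secondary outcomes, so Table 2 is the defining list. The Statistical methods section describes how outcomes are analysed, and its label borrows the drug that Table 2 gives as an example. The safety tabulation and the monitoring committee's report are not limited to isoniazid, and resistance to both drugs counts under either wording. This may well be what was intended, and it limits the harm. It does not remove the mismatch: an analyst who follows the Statistical methods section would leave out an isolate that Table 2 includes.

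A reader might infer more than this, in three ways.

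- *That resistance is tied to each participant's own regimen, so that cases are counted about 3.7 times as readily in the CRP arm.* Table 2 does not say so. The neighbouring row for TPT recipients and the DST condition in Outcomes make that reading possible, but a single list for the whole trial fits the words equally well and treats both arms alike. The ratio of 3.67 is expected 3HP exposure; it becomes a counting ratio only under the per-participant reading and equal underlying risk.
- *That rifamycin resistance would be hidden altogether.* Only rifamycin resistance without isoniazid resistance drops out, and only from the outcome in the analysis text.
- *That one or two cases would change the result.* With no resistance rate, margin or power stated for this outcome, the documents cannot support that.

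**Conclusion.** The inconsistency stands. As written in the analysis text, the outcome omits incident TB that is rifamycin-resistant but isoniazid-susceptible, although the trial gives a rifamycin as study TPT, tests for rifamycin resistance, and expects about 473 against at most 129 of 860 participants to start 3HP. Unequal counting between arms is conditional: it follows only if Table 2 is read per participant.

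The size of the effect is unknown. The case counts above rest on an assumed rate and show direction, not magnitude. The matter is confined to a secondary, safety-relevant outcome; the primary endpoint, sample size and power do not change. It is worth correcting because the outcome measures a harm that the protocol itself names, and because the correction is cheap.

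**What to change.** 1. Use one definition in Table 2, in the secondary-outcome text of Statistical methods and in the safety tabulation: DST-detected resistance to isoniazid and/or any rifamycin, in any participant with a DST result, whatever TPT that participant did or did not take.
2. Report isoniazid, rifamycin and combined resistance separately by randomized arm. Keep the Table 2 row restricted to TPT recipients as supporting description.
3. Reconcile Outcomes (DST for TPT recipients) with Final TB status assessment (no such limit). For the by-arm comparison to be even, DST must not depend on TPT receipt.

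**Cost.** Items 1 and 2 are wording and table layout; the DST panel already covers both drug classes. Item 3 costs nothing if Final TB status assessment already governs. If Outcomes governs, it adds DST on month-24 positive cultures from participants without TPT. The planned incident TB total of about 55.2 + 35.9 = 91 cases in both arms is a ceiling for this. The true number would be smaller, since some cases will be diagnosed before month 24, some will lack a positive culture, and some will be in TPT recipients who are tested anyway.
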